# The clinical value of mNGS of bronchoalveolar lavage fluid versus traditional microbiological tests for pathogen identification and prognosis of severe pneumonia (NT-BALF):study protocol for a prospective multi-center randomized clinical trial

**DOI:** 10.1186/s13063-024-08112-x

**Published:** 2024-04-22

**Keywords:** Severe pneumonia, mNGS, Traditional microbiological tests, Bronchoalveolar lavage fluid, Cost-effectiveness

## Abstract

**Background:**

Early, rapid, and accurate pathogen diagnosis can help clinicians select targeted treatment options, thus improving prognosis and reducing mortality rates of severe pneumonia. Metagenomic next-generation sequencing (mNGS) has a higher sensitivity and broader pathogen spectrum than traditional microbiological tests. However, the effects of mNGS-based antimicrobial treatment procedures on clinical outcomes and cost-effectiveness in patients with severe pneumonia have not been evaluated.

**Methods:**

This is a regional, multi-center, open, prospective, randomized controlled trial to evaluate that whether the combination of mNGS and traditional testing methods could decrease 28-day call-cause mortality with moderate cost-effectiveness. A total of 192 patients with severe pneumonia will be recruited from four large tertiary hospitals in China. Bronchoalveolar lavage fluid will be obtained in all patients and randomly assigned to the study group (mNGS combined with traditional microbiological tests) or the control group (traditional microbiological tests only) in a 1:1 ratio. Individualized antimicrobial treatment and strategy will be selected according to the analysis results. The primary outcome is 28-day all-cause mortality. The secondary outcomes are ICU and hospital length of stay (LOS), ventilator-free days and ICU-free days, consistency between mNGS and traditional microbiological tests, detective rate of mNGS and traditional microbiological tests, turn-out time, time from group allocation to start of treatment, duration of vasopressor support, types and duration of anti-infective regimens, source of drug-resistant bacteria or fungi, and ICU cost.

**Discussion:**

The clinical benefits of mNGS are potentially significant, but its limitations should also be considered.

**Trial registration:**

ChineseClinicalTrialRegistry.org, ChiCTR2300076853. Registered on 22 October 2023.

**Supplementary Information:**

The online version contains supplementary material available at 10.1186/s13063-024-08112-x.

## Introduction

### Background

Severe pneumonia caused by various pathogenic microorganisms is a leading cause of hospitalization and death worldwide [1]. The inappropriate application of antibiotics for pneumonia at early stages is the major reason for the increased morbidity and mortality rates [2]. If treatment is delayed, severe pneumonia can progress to multiple organ dysfunction and even death. Despite significant advances in etiological research and antimicrobial treatment, severe pneumonia remains the leading cause of death from infectious diseases worldwide [3]. In addition to the necessary mechanical ventilation, early, rapid, and accurate pathogen diagnosis can help clinicians select targeted treatment options, thus improving prognosis and reducing mortality rates [4].

Traditional microbiological tests include smear, culture, serology, and limited molecular panels. These methods are unable to identify the full range of potential pathogens (e.g., fastidious or nonculturable organisms or uncommon organisms not included in current panels). In addition, in many clinical laboratories, culture is very time consuming, requiring a 3–5-day wait time to get an accurate report. Serological testing and PCR require a priori assumption about the presence of a particular virus and require the laboratory to have the appropriate commercial kit. These conditions often lead to missed detection of certain pathogens [5]. Previous studies have shown that metagenomic next-generation sequencing (mNGS) has a higher sensitivity and broader pathogen spectrum than traditional microbiological tests. Recently, the possibility of using mNGS to identify non-sterile site specimens in the respiratory tract has been discussed. mNGS is assumed to optimize antibiotic treatment in critically ill patients with infectious diseases. While helpful, little is known about how to interpret the application of mNGS results in lower respiratory tract infections (LRTIs), which leads to conflicting opinions, as mNGS does not elucidate whether the organism is viable or a pathogen. Incorrect interpretation or false positive results perhaps escalate antimicrobial regimen [6]. This may result in inappropriate treatment, which may prolong or aggravate the status of disease. In particular, prospective clinical trial and economic data showing the cost-effectiveness of these relatively expensive tests in improving patient outcomes are needed to justify their use.

#### Objectives

Recently, the possibility of using mNGS to identify non-sterile site specimens in the respiratory tract has been discussed, though there are still conflicting opinions. The purpose of this study is to evaluate the effectiveness and consistency of bronchoalveolar lavage fluid (BALF) mNGS in diagnosing and treating pulmonary infections in comparison to conventional testing methods. Furthermore, the aim is to demonstrate whether the combination of mNGS and traditional testing methods could decrease 28-day all-cause mortality with moderate cost-effectiveness.

## Method

### Study design

This study is a regional, multi-center, open, prospective, randomized controlled trial that will include patients with severe pneumonia, from four large tertiary hospitals in North China. A total of 192 participants will be enrolled and randomly assigned in a 1:1 ratio to either the study group (mNGS combined with traditional microbiological tests group) or the control group (traditional microbiological tests group) using the central randomization system. Patients will be provided anti-infective treatment based on clinical experience according to mNGS + traditional tests or traditional tests only for two groups. The NT-BALF trial will be conducted according to the principles of the Declaration of Helsinki [7]. The Institutional Review Board of Peking Union Medical College Hospital, Chinese Academy of Medical Sciences & Peking Union Medical College in Beijing, China, approved the trial protocol (version 4.0, reference number I-23PJ1316, date 15 August 2023). The flowchart of the protocol is shown in Fig. 1. The schedule of enrolment, intervention, and assessments following the Standard Protocol Items: Recommendation for Interventional Trials (SPIRIT) guidelines (Additional file 1) is presented in Fig. 2.

**Fig. 1 Fig1:**
[figure not shown]
Flowchart of the study protocol

**Fig. 2 Fig2:**
[figure not shown]
The schedule of enrolment, intervention and assessments. TMT, traditional microbiological tests; EOT, end of therapy; E, discharge from the ICU. “*” symbol indicates baseline variables: age, gender, BMI (body mass index), history of smoking, comorbidity, etc. “^” symbol indicates primary outcome: 28-day all-cause mortality. “^#^” symbol indicates secondary outcome: (1) ICU and hospital length of stay (LOS), (2) ventilator-free days and ICU-free days, (3) consistency between mNGS and traditional microbiological tests, (4) detective rate of mNGS and traditional microbiological tests, (5) turn-out time, (6) types and duration of anti-infective regimens, (7) source of drug-resistant bacteria or fungi, and (8) ICU cost

### Inclusion criteria and exclusion criteria

Inclusion criteria are (1) patient aged ≥ 18 years, (2) diagnosis of severe pneumonia and admitted to an ICU, and (3) time from severe pneumonia diagnosis to ICU admission < 48 h. Severe pneumonia was defined in patients with either one major criterion or at least three minor criteria of the Infectious Diseases Society of America (IDSA)/American Thoracic Society (ATS) criteria [8]. Major criteria are as follows: (1) septic shock with need for vasopressors and (2) respiratory failure requiring mechanical ventilation. Minor criteria are as follows: (1) respiratory rate > 30 breaths/min, (2) PaO_2_/FIO_2_ ratio < 250, (3) multi-lobar infiltrates, (4) confusion/disorientation, (5) uremia (blood urea nitrogen level > 20 mg/dl), (6) leukopenia (white blood cell count < 4000 cells/ml), (7) thrombocytopenia (platelet count < 100,000/ml), (8) hypothermia (core temperature < 36 °C), (9) hypotension requiring aggressive fluid resuscitation. Informed consent will be obtained from all the patients or their guardians before enrollment. Participants will be excluded if they are (1) aged < 18 years, (2) pregnant or lactating, (3) are expected to die within 24 h, (4) diagnosed with HIV, or (5) are receiving palliative therapy or supportive treatment only.

### Participant recruitment

Participants will be recruited from four medical centers in tertiary hospitals in North China including Peking Union Medical College Hospital, Beijing Chao-yang Hospital, Tianjin Medical University General Hospital, and The Second Hospital of Hebei Medical University. There is a research coordinator at each hospital to promote and coordinate the trial. Patients will be informed of the purpose and procedures involved and the potential risks and benefits of the study. The participants’ written consent will be obtained. Participants will be allowed to withdraw from the trial at any time without consequence.

Each branch center will post printed recruitment posters inside and outside the hospital. Patients with severe pneumonia will be invited to participate in this study once after diagnosis. At the screening visit, a trained research staff (physicians) will confirm the eligibility by the symptom, laboratory result, and chest X-ray or CT image and check every inclusion and exclusion criterion. The recruitment time is 36 months, from November 2023 to October 2026.

### Randomization and blinding

Stratified block randomization will be performed centrally in a 1:1 ratio using the SAS software (SAS Institute, Inc., Cary, NC, USA). Within each stratum, a random block size of 4 will be used. Considering the nature of antibiotic intervention, this study is open to the clinicians, patients, and investigator; only the data analyst and follow-up evaluator will be blinded.

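### If 4 is the only block size, up to one third of allocations within a stratum can be deduced in this open-label trial, and calling that size random is contradictory

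*Protocol article*

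**What the plan says.** The Study design section assigns patients 1:1 "using the central randomization system". The Randomization and blinding section adds "Stratified block randomization will be performed centrally in a 1:1 ratio using the SAS software", followed by "Within each stratum, a random block size of 4 will be used". No other block size is given, and the strata are not named.

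On blinding, the same section says "this study is open to the clinicians, patients, and investigator; only the data analyst and follow-up evaluator will be blinded".

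On enrolment, the Participant recruitment section says "Participants will be recruited from four medical centers in tertiary hospitals in North China" and that "a trained research staff (physicians) will confirm the eligibility". The exclusion criteria include patients who "are expected to die within" 24 hours. The primary outcome is death from any cause by day 28.

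The article was published on 22 April 2024. Recruitment is planned for 36 months, from November 2023 to October 2026.

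**The concern.** A random block size means that the size is drawn from several values so that nobody can tell where a block ends. With one size there is nothing to draw. The sentence may mean randomly permuted blocks of fixed size 4, or it may be a garbled account of varying sizes. It cannot be right as written, and 4 is the only size it gives.

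A fixed, known size matters most in an open trial. Whoever sees the arms of earlier patients can count how many places each arm has left in the current block. In a block of 4 the last place is always determined, and so is the third when the first two went to the same arm. By the planned dates, the block size has been public for about 30 of the 36 recruitment months.

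At stake is who enters each arm. Expected death within 24 hours is a judgement of prognosis and lies close to the primary outcome. A physician who knows the next arm could apply it more or less strictly, even without intending to. Blinding the data analyst and follow-up evaluator does not help, because this bias enters before randomization. Intention-to-treat analysis does not remove it either.

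**Working it through.** The article states no predictability figure, so there is none to reproduce. The inputs are block size 4, ratio 1:1 and total 192, all from the article.

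**Allocations known with certainty, fixed block of 4.** There are 6 possible blocks (AABB, BBAA, ABAB, BABA, ABBA, BAAB) with 6 × 4 = 24 positions. A position is forced when one arm has already used both its places.
- AABB and BBAA have 2 forced positions each: 2 × 2 = 4.
- The other four blocks have 1 each: 4 × 1 = 4.
- Share forced: (4 + 4)/24 = 8/24 = 33.3%.
- Over the whole trial: 192/3 = 64 patients on average.
- If strata are the four centres and they recruit equally (both assumed): 192/4 = 48 per centre, of which 48/3 = 16 are forced.

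**Best-guess success, fixed block of 4.** The guess is always the arm with more places left, and a coin toss when they are equal.
- Position 1: 1/2.
- Position 2: 2/3.
- Position 3: 1/3 × 1 + 2/3 × 1/2 = 2/3.
- Position 4: 1.
- Mean: (0.500 + 0.667 + 0.667 + 1.000)/4 = 70.8%, against 50% without blocks.

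**Other schemes.** Fixed sizes were enumerated in the same way. Mixed sizes were simulated with 3000 sequences of 48 patients. The guesser knew the set of sizes but not their order, and updated the probabilities after each allocation. The mixes are illustrations and do not come from the article.

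| Block sizes | Known with certainty | Best guess correct |
|---|---|---|
| 4 | 33.3% | 70.8% |
| 6 | 25.0% | 68.3% |
| 8 | 20.0% | 66.6% |
| 2 and 4 mixed | about 11% | about 72% |
| 2, 4 and 6 mixed | about 4.1% | about 70% |
| 4 and 6 mixed | about 5.6% | about 69% |
| 4, 6 and 8 mixed | about 2.2% | about 68% |

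Varying the size removes most of the certainty but little of the guessing advantage. Adding blocks of 2 does not help with guessing: the 2 and 4 mix does slightly worse than fixed 4.

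**Cost in balance.** If recruitment stops inside a block of size b, the arms in that stratum can differ by at most b/2. That is 2 for blocks of 4 and 4 for a final block of 8.

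**The case against.** The strongest reply is that randomization is central. The list and the next assignment are withheld from sites, and this stands. A reader might infer that allocation is not concealed at all, but the Study design and Randomization and blinding sections do not support that. The defect is partial predictability.

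One third is also a ceiling. It needs a recruiter who knows every earlier allocation in the stratum and where each block began. The article says that the trial is open to clinicians and investigators, not that any of them tracks the sequence. It does not say that the physicians who confirm eligibility are the treating clinicians. The strata are unnamed, which an article may leave to the full protocol. If strata are centres, tracking is plausible. If a stratum spans centres, or further factors divide each centre, it is harder. This stands as a limit on the size of the problem.

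A reader might also infer that enrolment could be delayed until a preferred slot comes up. The Intervention section requires lavage within 24 hours of ICU entry. Planned accrual is 192/(4 × 36) = 1.3 patients per centre per month if centres recruit equally (assumed). Waiting for another slot is hardly feasible, so the realistic route is selective non-enrolment.

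Finally, the wording may simply be loose, and sizes may in fact vary. In that case only the sentence is wrong. The article cannot settle this.

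**Conclusion.** The point holds in a limited form. The sentence contradicts itself and needs correction whichever meaning was intended. If 4 is the only size, up to 33.3% of allocations within a stratum (about 64 of 192) are deducible and best guesses succeed 70.8% of the time. Both figures assume full knowledge of earlier allocations and block starts in the stratum. This weakens, but does not abolish, the protection of central randomization, and it opens a route to selective enrolment in an open trial with a mortality endpoint.

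A reader might want to turn the 64 deducible slots into a shift in the mortality difference, to set beside the planned 15% against 33%. The article gives no basis for how many slots would be recognised and acted on, or for how far baseline risk would then differ between arms. No size of bias can be stated.

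The change should be made because it is cheap and recruitment is planned to run to October 2026, but the article does not show that bias has occurred.

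**What to change.** - If 4 is the only size in use, generate the unused part of the central list with randomly varying block sizes within each stratum, for example 4, 6 and 8.
- Keep the sizes out of every document that sites can see. The article says that substantial amendments are notified to the research coordinators, who work at the hospitals, so that notice should say that the scheme changed without giving the sizes.
- Reword the sentence to say that permuted blocks of varying, undisclosed size are used.
- If sizes already vary, only the sentence needs correction.

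The cost is one regeneration of the remaining list and one amended sentence. Endpoints, sample size and analysis stay as they are. The possible imbalance at the end rises from 2 to at most 4 per stratum.

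The gain should not be oversold. With a 4, 6 and 8 mix, certain knowledge falls from 33% to about 2%, but best-guess success falls only from 70.8% to about 68%. Certainty is the part most easily exploited, so the change is still worth making.

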### Intervention

For both groups, bronchoalveolar lavage fluid will be harvested within 24 h of participants entering the ICU. Traditional microbiological tests will be collected as soon as possible after admission and will be performed in local in-house laboratories. Traditional microbiological tests, including culture, antigen detection, multiplex PCR, and direct microscopic examination of specimens. The results of traditional microbiological tests will be interpreted according to standard procedures.

BALF specimens will be divided into aliquots and used for both mNGS tests and traditional microbiological tests for study group. BALF mNGS tests will be transferred to the same professional genomic laboratory independently by cold chain transportation. The genomic laboratory will perform nucleic acid extraction, library construction, amplification and sequencing, bioinformatic analysis, and data interpretation according to previous clinical practice.

In the study group, anti-infective treatment regimen is based on both BALF mNGS and traditional microbiological tests, while in the control group, it is based on the results of traditional microbiological tests. The results of mNGS and necessary clinical data will be judged by a group of senior clinicians, who reached a unified opinion.

### Data measurement

Clinical data will be collected locally on an electronic case report form (CRF). The research coordinator at each hospital will provide training in study procedures to improve adherence to the protocol. Furthermore, they will check CRFs and contact responsible staff members to ensure data quality.

### Outcomes

The primary outcome is 28-day all-cause mortality. The secondary outcomes are (1) ICU and hospital length of stay (LOS), (2) ventilator-free days and ICU-free days, (3) consistency between mNGS and traditional microbiological tests, (4) detective rate of mNGS and traditional microbiological tests, (5) turn-out time, (6) types and duration of anti-infective regimens, (7) time from group allocation to start of treatment, (8) duration of vasopressor support, (9) source of drug-resistant bacteria or fungi, and (10) ICU cost.

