### Quality control

A data monitoring committee, comprising physicians, an intensivist, a microbiologist, a statistician, and quality management personnel, will be established. Before the study begin, the principal investigators will accept good clinical practice (GCP) training, and all researchers will accept training including study protocol, informed consent, case report form, standard operating procedures of participants’ data collections, and collection and preservation methods of biological samples to ensure the trail quality. They not only determine the methods of clinical trials but also solve major problems encountered in practical applications. Participants will accept bronchoscopy by trained respiratory physician to acquire lower respiratory samples within 24 h. Biological samples for mNGS testing will be transferred to the same professional genomic laboratory (Vision Medicals Center for Infectious Diseases) independently by cold chain transportation. During the study, samples for traditional microbiological testing will be conducted by trained specialists of local in-house laboratories with standard procedure.

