Studies regarding the cost-effectiveness of mNGS assays for pathogen detection are lacking. Relative to most traditional microbiological tests, mNGS testing is expensive. The incremental costs of testing are minimal, compared to the costs of intensive care unit stays or myriad diagnostic tests, not to mention use of even more expensive and advanced anti-infective drugs that are ordered for complex cases. Our study will evaluate the cost-effectiveness data of mNGS testing in severe pneumonia.

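### ICU cost is the only cost outcome, but the cost-effectiveness aim is tied to 28-day mortality in any location, so ward costs after ICU discharge are left out

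*Protocol article*

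**What the plan says.** The Objectives section sets a joint aim on survival and cost: whether mNGS added to traditional testing "could decrease 28-day all-cause mortality with moderate cost-effectiveness". The Abstract repeats this aim, and the Discussion makes a promise: "Our study will evaluate the cost-effectiveness data of mNGS testing in severe pneumonia".

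The effect side is fixed in Outcomes: "The primary outcome is 28-day all-cause mortality". It is not restricted to deaths in the ICU. The secondary list opens with stay in both settings: "The secondary outcomes are (1) ICU and hospital length of stay (LOS").

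The cost side is one item, and it is the same in all three places where outcomes are listed:
- Outcomes: "9) source of drug-resistant bacteria or fungi, and (10) ICU cost"
- Abstract, Methods: "source of drug-resistant bacteria or fungi, and ICU cost"
- Fig. 2 caption: "7) source of drug-resistant bacteria or fungi, and (8) ICU cost"

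No hospital cost, total cost or separate test cost is listed, and the content of ICU cost is not described.

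On the test itself, Quality control states: "Biological samples for mNGS testing will be transferred to the same professional genomic laboratory". According to Intervention, traditional tests are run in each hospital's own laboratory. The Discussion calls mNGS expensive relative to most traditional tests but gives no price.

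**The concern.** A cost-effectiveness statement needs cost and effect over the same period and the same settings. Here benefit is counted to day 28 in any location, while cost is counted only in the ICU. A patient who leaves the ICU alive on day 10, for example, contributes benefit to day 28 but no further cost.

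Two consequences follow. First, survivors go on to use ward care and patients who die in the ICU do not, so an intervention that saves lives generates costs that the measure cannot see. Second, an earlier transfer to the ward lowers ICU cost even when the total hospital bill is unchanged, so a shift of cost is recorded as a saving. Both can make the study group look cheaper than it is. Economic value is half of the trial's stated aim, and the Background gives the lack of economic data as a reason for doing the trial.

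**Working it through.** **Inputs.** Planned 28-day mortality is 33% in the control group and 15% in the study group (Sample size). The total is 192, so 192/2 = 96 per group. The document contains no prices, and none are supplied here.

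**The plan's own figure.** There is no cost figure to reproduce. The mortality difference used below is the one behind the sample size: (1.960 + 0.842)² × (0.15 × 0.85 + 0.33 × 0.67) / 0.18² = 7.849 × 0.3486 / 0.0324 = 84.4, rounded up to 85 per group, as stated. The present point does not depend on that calculation beyond the difference 0.33 − 0.15 = 0.18.

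**Boundaries side by side.**

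| Quantity | Setting counted |
|---|---|
| Cost | ICU only |
| Effect (death) | Any location, to day 28 |
| Length of stay | ICU and hospital |

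The cost boundary is narrower than both of the others.

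**Error in a cost per death averted.** The article defines no ratio, so this one is used only to show the mechanism. Let D be the mean ward cost per patient in the study group minus that in the control group. Leaving ward cost out makes the result too low by D / 0.18. A negative D makes it too high.

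*Extra survivors.* Assume that deaths occur in the ICU and that a survivor's mean ward cost W is the same in both groups. Then D = 0.85W − 0.67W = 0.18W, and the error is 0.18W / 0.18 = W, one survivor's whole ward cost. In patients, 0.18 × 96 = 17.3, so about 17 additional survivors would have uncounted ward stays.

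*Earlier transfer.* Assume that an amount T per study patient moves from ICU to ward with the total unchanged. On ICU cost alone the result is −T / 0.18 = −5.6T, an apparent saving. On total cost it is 0.

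**Illustration in assumed units** (mean control ICU cost = 100; all cost differences assumed, study minus control):

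| ICU difference | Ward difference | mNGS fee not in ICU cost | ICU cost only | All items |
|---|---|---|---|---|
| 0 | 5 | 0 | 0 | 5/0.18 = 27.8 |
| 0 | 10 | 0 | 0 | 10/0.18 = 55.6 |
| −5 | 5 | 0 | −5/0.18 = −27.8 | 0 |
| −5 | 10 | 0 | −27.8 | 5/0.18 = 27.8 |
| −5 | 5 | 2 | −27.8 | 2/0.18 = 11.1 |

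The sign can change. This shows what is possible, not what is expected.

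**The mNGS fee, conditionally.** If a fee F per study patient were not contained in ICU cost, a cost per death averted would be understated by F / 0.18 = 5.6F.

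**The case against.** The strongest reply is that an ICU perspective is a recognisable choice. All participants are ICU patients, the Discussion itself weighs test cost against the cost of ICU stays, and hospital length of stay is recorded, so ward days could be costed later. Costing detail also commonly sits in a full protocol or analysis plan that is not shown here. Part of this stands: the article owes the reader no costing manual. But the choice of cost outcome is not a detail left for later. It is stated three times in the same form, and it is narrower than the aim it serves. Recorded ward days are a resource count, and nothing in the article says they will be priced.

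Several stronger readings are tempting and are not supported:

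- *That the mNGS fee is left out.* The outside laboratory shows where the test is run, not where it is billed. Lavage fluid is taken within a day of ICU entry, so the fee may well be part of ICU cost. The document does not settle it, and the 5.6F figure is conditional.
- *That ICU cost is distorted by spending before allocation.* No start point for cost is stated, and randomisation balances such spending in expectation.
- *That Fig. 2 places the cost assessment at ICU discharge.* The figure is not available here. Its caption defines a code for ICU discharge but does not link cost to it.
- *That a stated cost-effectiveness result is wrong.* The article states an aim and defines no ratio.

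**Conclusion.** The point holds in this form: the only cost outcome excludes costs after ICU discharge, while the effect it is to be weighed against runs to day 28 in any setting. Followed as written, additional survivors' ward stays are not counted, and earlier transfer to the ward appears as a saving.

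The size in money cannot be computed. The statement that a cost per death averted would be too low by one survivor's ward cost rests on the planned 33% and 15%, on deaths occurring in the ICU, and on similar ward costs per survivor in both groups. If mNGS also shortened ward stays, ICU cost could instead miss a saving, so the direction is likely rather than certain.

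The matter concerns one secondary outcome and the cost-effectiveness part of the aim. The primary outcome, the sample size and safety are unaffected. It is a cheap improvement worth making, not a flaw in the mortality comparison.

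**What to change.** Use total hospital cost from randomisation to day 28, or to hospital discharge if earlier, in both groups as the cost input to the cost-effectiveness evaluation. Keep ICU cost as a reported component. Enter the mNGS fee and its cold-chain transport as an explicit line for each study-group patient, and make sure it is counted only once if the ICU bill already contains it. Check that the cost assessment time in Fig. 2 matches the new window. Make the same change in the Abstract, Outcomes and the Fig. 2 caption.

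The price is slightly more data collection: hospital charges to day 28 and one added line on the case report form. The article does not describe a billing source, so its availability at the four hospitals has to be confirmed. Total hospital cost is likely to be more variable than ICU cost, and costs of stays beyond day 28 are cut off. That cut-off matches the window of the primary outcome.
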